### Primary outcomes

The primary outcomes are quality of life, walking speed, and postural sway. All primary outcomes will be aggregated according to their mean and the outcome will be assessed as a change from the baseline. Table 2 lists the main characteristics of the primary outcomes according to their elements as in Saldanha et al. [24].

**Table 2 Tab2:** Elements of the completely specified primary outcomes

Domain	Measurement	Metric	Aggregation	Time-point
Quality of life	SF-12	Change from baseline	Mean	At week 12 (end of treatment) At week 48 (end of follow-up)
Walking speed	Gait analysis	Change from baseline	Mean	At week 12 (end of treatment)
Postural sway area	Stabilometry	Change from baseline	Mean	At week 12 (end of treatment)

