### Power analysis and statistical analysis

Sample size for expected difference in the primary outcome was based on pilot trials. Effect size of treatment on various outcomes, including motor skills, was 0.48 mean of the standard deviation (SD), with 95% CI = 0.10 to 0.85. As for quality of life and mood, we aimed at detecting clinically significant changes induced by moderate physical exercise. In a recent meta-analysis, moderate-to-vigorous physical exercise was associated with a medium effect size of 0.64 (95% CI, 0.27 to 1.01) in reducing depressive symptoms [26]. Overall, we expect that the experimental intervention could produce a change in the exposed group with an effect size of 0.45 SD. We have determined, by a test of difference between proportions, that a sample of 60 participants per group is required to achieve 80% power to detect a difference with a medium effect size *h* = 0.45, at a two-sided significance level of 0.05. It means that at the estimated power, risk reduction is 0.215, and number needed to treat (NNT) = 5.

The main outcome measures and expected improvement are the following: SF-12 score (10%), walking speed (10%), and postural sway area (20%). Differences in the primary outcomes will be analyzed with a two-tail test for proportions with the Miettinen exact test. A multiple logistic regression will be performed to treat the confounding factors and control the impact of the confounding variables (sex, age, co-morbid condition, previous exercise activity) on outcomes. Survival analyses will be carried out using the Kaplan-Meier curve. Data will be analyzed at the individual level, and clustering (participants having been exposed to the intervention in groups) will be not accounted for in the analysis. Analysis by treatment allocated will be used considering both primary and secondary outcomes. The analysis by treatment allocated will include all participants for which there is data at t0. There will be no interim analyses planned for efficacy or safety since this is a short trial with no administered drug. Analyses will be done with Excel or the Statistical Package for Social Science (SPSS).

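### The primary outcomes are defined as mean change from baseline but tested and powered as proportions, with 0.45 SD carried over as h = 0.45

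*Protocol article*

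**What the plan says.** In the protocol article, the section on primary outcomes states: "All primary outcomes will be aggregated according to their mean and the outcome will be assessed as a change from the baseline". Table 2 repeats this for SF-12, walking speed and postural sway area, with change from baseline as the metric and the mean as the aggregation. Week 12 is a primary time point for all three outcomes; week 48 is a further one for SF-12.

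The section on power and statistical analysis works with proportions:
- The effect is introduced on a mean scale: "we expect that the experimental intervention could produce a change in the exposed group with an effect size of 0.45 SD".
- The sample size uses a test of proportions, "to detect a difference with a medium effect size *h* = 0.45", "at a two-sided significance level of 0.05". It concludes that "a sample of 60 participants per group is required to achieve 80% power" and that "risk reduction is 0.215, and number needed to treat (NNT) = 5".
- The primary test is: "Differences in the primary outcomes will be analyzed with a two-tail test for proportions with the Miettinen exact test".
- Adjustment is by multiple logistic regression on "sex, age, co-morbid condition, previous exercise activity". The baseline value of the outcome is not on this list.
- Figures of 10%, 10% and 20% are given for the three outcomes, but as the improvement anticipated, not as a threshold that classifies a participant.

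**The concern.** A difference in mean change cannot be put into a test of proportions or a logistic regression. Each participant would first have to be classified as improved or not, and the article gives no rule for that. The analyst would have to invent a cut-off or change the test, so the primary result on all three outcomes stays open to choice after the data are seen.

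The sample size has the same fault. A standardized mean difference of 0.45 and an arcsine difference h of 0.45 are different quantities, and splitting a continuous measure loses information. The trial could be planned around a power that its stated test does not have for its stated effect.

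**Working it through.** **Inputs from the article:** 60 per group, 1:1 allocation, two-sided 0.05, expected effect 0.45 SD, h = 0.45, risk difference 0.215.

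**Assumptions made here:** normal outcomes with equal variances, no dropout, and the baseline/follow-up correlations r given below.

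**1. The plan's own figure.** For Cohen's h, n per group = 2 × [(z_α + z_β)/h]².
- Two-sided: 2 × [(1.960 + 0.842)/0.45]² = 77.5, so 78 per group.
- Power at 60: Φ(0.45 × √30 − 1.960) = Φ(2.465 − 1.960) = 69%.
- One-sided 0.05 comes close to the stated figure: 2 × [(1.645 + 0.842)/0.45]² = 61.1, and power at 60 is 79%. The article says two-sided.
- The risk difference of 0.215 (1/0.215 = 4.65, so NNT 5) fits an h of about 0.44, for example 50% against 71.5%. That pair needs 80 per group and has 68% power at 60.

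**2. What 0.45 SD becomes after a split.** With control responder rate p_c, the treated rate is p_t = Φ(Φ⁻¹(p_c) + 0.45). Then h = 2·arcsin√p_t − 2·arcsin√p_c, and power = Φ(h√30 − 1.960). Here 0.45 is in SDs of the change score.

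| Control rate | Treated rate | Difference | h | Power, 60 per group |
|---|---|---|---|---|
| 10% | 20.3% | 0.103 | 0.291 | 36% |
| 20% | 34.8% | 0.148 | 0.334 | 45% |
| 41.1% (best cut) | 58.9% | 0.178 | 0.358 | 50% |
| 50% | 67.4% | 0.174 | 0.355 | 49% |

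The best cut gives h = 0.36 and a risk difference of 0.18, not 0.45 and 0.215. Exact enumeration over cut points gives maximum power of 44% (Fisher), 49% (exact unconditional score test) and 52% (asymptotic Miettinen–Nurminen). At the best cut, 123 per group would be needed for 80%.

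**3. Comparing mean change directly.** A t-test with d = 0.45 and 60 per group has 69% power (noncentral t, 0.686).

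**4. If 0.45 is in raw-score SDs.** The effect in change-score SDs is then 0.45/√(2(1 − r)).

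| Assumed r | Effect in change SDs | Best-cut proportions | t-test on change |
|---|---|---|---|
| 0.3 | 0.380 | 38% | 54% |
| 0.5 | 0.450 | 50% | 69% |
| 0.6 | 0.503 | 59% | 78% |
| 0.7 | 0.581 | 71% | 88% |

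**5. Adding the baseline value as a covariate (a separate matter).** The ANCOVA effect size is 0.45/√(1 − r²) if 0.45 is in raw SDs, and 0.45 × √(2/(1 + r)) if it is in change SDs.
- r = 0.5: 0.520 on both readings, power 81%.
- r = 0.7: 0.630 (raw), power 93%; 0.488 (change), power 76%.

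**The case against.** Four things can be said on the other side.

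- **The 50% is conditional.** A reader might infer that power is at most 50% whatever the circumstances. The article does not say which SD the 0.45 refers to. The change-score SD is the natural reading because the metric is change, but on the raw-score reading best-cut power reaches 59% at r = 0.6 and 71% at r = 0.7. This stands, so the 50% must be quoted with its assumption.
- **Missing baseline adjustment does not cause the drop.** A reader might blame the fall from 69% to 50% partly on the covariate list. It comes from dichotomising alone. A change score already uses the baseline value, and adding that value as a covariate is a further gain in efficiency. This also stands.
- **ANCOVA's advantage can be exaggerated.** Setting 93% beside 50% mixes two SD scales. On one scale at r = 0.7 the comparison is 76% with 50%, or 93% with 71%.
- **Analysis detail may sit in a plan not shown.** This would answer a point about omitted detail. It does not answer this one, because the article fixes both the outcome summary and the test, and they are incompatible.

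A reader might also take 10%, 10% and 20% as responder cut-offs. The article never uses them that way.

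**Conclusion.** The mismatch between outcome definition and primary test is real and affects all three primary outcomes. So is the equating of 0.45 SD with h = 0.45.

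The size depends on an SD that the article leaves unstated. With change-score SDs, normality and no dropout, the stated test has about 50% power at its best cut and 36% at a 10% control responder rate; a t-test on mean change has 69%. With raw-score SDs the levels move with the correlation, but dichotomising costs 16 to 19 points at every value checked from 0.3 to 0.7.

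The right benchmark is 69%, not 80%: the stated power does not reproduce as a two-sided calculation even if h = 0.45 is granted. Omitting the baseline value from the covariates is a separate and lesser point. The sponsor needs to resolve the contradiction before the primary analysis.

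**What to change.** - Make the primary analysis of each primary outcome an ANCOVA of the value at each primary time point in Table 2: week 12 for all three, and also week 48 for SF-12. The terms are allocated group, the baseline value of that outcome, and the covariates already listed. Report the adjusted mean difference with its 95% CI.
- Keep responder proportions as a secondary analysis, with cut-offs fixed in advance.
- Restate power for d = 0.45 at 60 per group, naming the SD: 69% unadjusted, with ANCOVA power shown over a range of assumed correlations.
- If the sponsor prefers proportions as primary, the consistent alternative is to define the responder cut-offs, rewrite the outcome section and Table 2 to match, and size the trial on the resulting proportions.

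**Cost.** No new data are needed, since baseline and outcome values are already scheduled. The responder rate and NNT become secondary. The change is more than wording: the trial status section plans the end of data collection for June 2020 and dates the protocol version April 2021. It must therefore be dated, justified and documented as made before unblinding. The masking of analysts to group identity, described under blinding, makes that possible.

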### Randomization

Randomization will be conducted at the University of Cagliari after baseline assessment. Randomization will be computer-based and concealed. The people who will conduct the randomization procedure are blind to the participants’ identities and status and will not receive any information on the participants. Randomization will be by blocks of randomized permutations to experimental treatment with a 1:1 rate; codes will be masked.

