### Treatment

After signing the informed consent, the enrolled subjects will be randomly allocated to experimental treatment by blocks of randomized permutations with a 1:1 rate; codes will be masked. Participants will be evaluated at time zero (t0), baseline; t1, week 12, end of the trial; t2, 24 weeks (circa 6 months) after end of trial; and t3, 48 weeks (circa 12 months) after the end. Blood samples will be conducted at t0 and t1 (3 daily samplings will be made to check the circadian changes). A questionnaire about exercise during the previous six weeks will be done at t0, t2 and t3 (see Table 1 for details; all items can be found in the protocol).

**Table 1 Tab1:** Schedule of enrolment, interventions, and assessments

	Study period						
Time point	tx	t0		12 weeks	t1	t2	t3
	Enrollment	Baseline	Allocation	Treatment	Post-testing	24 week F-U	48 week F-U

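### The primary comparison leaves out four named baseline covariates, which enter only a separate logistic model justified, wrongly in a randomised trial, as dealing with confounding

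*Protocol article*

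**What the plan says.** All of the analysis text is in the protocol article, section Power analysis and statistical analysis. The primary test is unadjusted: "Differences in the primary outcomes will be analyzed with a two-tail test for proportions with the Miettinen exact test". The next sentence introduces the model: "A multiple logistic regression will be performed to treat the confounding factors and control the impact of the confounding variables", with the variables listed as "sex, age, co-morbid condition, previous exercise activity) on outcomes". The article does not say whether this model is primary or supportive, or how its result is to be read beside the unadjusted one.

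The section Randomization describes a computer-based, concealed procedure: "Randomization will be by blocks of randomized permutations to experimental treatment with a 1:1 rate". On timing it says: "Randomization will be conducted at the University of Cagliari after baseline assessment". Table 1 places demography and the medical assessment at enrolment and the IPAQ at baseline, so the four variables appear to be measured before allocation.

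The only effect given on a binary scale is in the sample-size paragraph: "risk reduction is 0.215, and number needed to treat (NNT) = 5". The section Primary outcomes, with Table 2, defines the same outcomes as mean change from baseline.

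**The concern.** Confounding of a treatment comparison needs a systematic link between the covariate and allocation. Concealed 1:1 randomisation removes that link, and only chance imbalance is left. The sound reasons to adjust are that the covariates predict the outcome and that chance imbalance can occur. The article gives neither reason.

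Two things follow. First, the odds ratio is non-collapsible: adding a covariate that predicts the outcome changes the quantity being estimated, even when the arms are identical on that covariate. A reader who takes the stated purpose at face value could credit the resulting gap to confounding that had been dealt with. Second, the covariates the investigators themselves regard as influential are left out of the comparison that tests the primary outcomes, which gives up whatever precision they carry.

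**Working it through.** **Inputs from the protocol.** 60 per arm, two-sided 0.05, risk difference 0.215, NNT 5, four covariates.

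**Assumptions, not in the protocol.** Control response 0.50 (0.20 to 0.50 also examined). The covariates combine into a normal score, perfectly balanced between arms, with SD s on the logit scale. As a guide to strength, s²/(s² + π²/3) is the share of latent variance explained: 0.25/(0.25 + 3.29) = 7% at s = 0.5 and 1/(1 + 3.29) = 23% at s = 1.0.

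**Step 1: the plan's own figure.** 1/0.215 = 4.65, which rounds to NNT 5. The two figures agree. With control response 0.50 the other arm is 0.50 + 0.215 = 0.715, and h = 2·arcsin(√0.715) − 2·arcsin(√0.50) = 0.444, close to the planned 0.45.

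**Step 2: unadjusted odds ratio.** (0.715/0.285)/(0.50/0.50) = 2.51.

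**Step 3: adjusted odds ratio with no imbalance.** For each s, find intercepts a0 and a1 such that the average of 1/(1 + exp(−(a + s·Z))) over a standard normal Z equals 0.50 and 0.715. The conditional odds ratio is exp(a1 − a0). At s = 1.0, a0 = 0 and a1 = 1.104, so it is exp(1.104) = 3.02, and 3.02/2.51 = 1.20.

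| s | Unadjusted OR | Conditional OR | Ratio |
|---|---|---|---|
| 0 | 2.51 | 2.51 | 1.00 |
| 0.25 | 2.51 | 2.54 | 1.01 |
| 0.5 | 2.51 | 2.64 | 1.05 |
| 1.0 | 2.51 | 3.02 | 1.20 |
| 1.4 | 2.51 | 3.48 | 1.39 |

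Control responses from 0.20 to 0.50 give nearly the same ratios (1.20 to 1.21 at s = 1.0). There is no confounding anywhere in this table.

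**Step 4: back to the risk scale.** Averaging the predicted response over all participants under each arm, from the same model, returns a risk difference of 0.215 at every s. The risk difference does not shift as the odds ratio does.

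**Step 5: single trials.** In 1,500 simulated trials per setting, with 60 per arm and an assumed control response of about 0.39, the adjusted log odds ratio was further from zero than the unadjusted one in 66% of trials at s = 0, 78% at s = 0.5 and 88% at s = 1.0. The shift is expected, but it does not occur in every data set.

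**Step 6: power at 0.50 against 0.715, 60 per arm.** An unadjusted score test has about 68%. A test of the standardised risk difference has about 69% at s = 0.3, 71% at s = 0.6, 76% at s = 1.0 and 82% at s = 1.4, with no gain at s = 0. The gain up to s = 1.0 is therefore 76 − 68 = 8 points at most. Simulation error and the choice of variance estimator move these figures by up to about two points. That 68% falls short of the planned 80% is a separate sample-size matter and plays no part here.

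**The case against.** The strongest reply is that the primary test is named, unadjusted and valid, and that adjusting for pre-specified covariates is good practice whatever it is called. Blocks are mentioned but stratification is not, so chance imbalance among 120 people is itself a fair reason to adjust. An unadjusted primary test with a supportive adjusted model is a standard choice. All of this stands. It makes the point an improvement in efficiency and clarity, not a correction of an invalid test.

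Several stronger readings are tempting, and the document does not support them:

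- **That the adjusted odds ratio will overstate the effect.** It is a valid estimate of a different quantity. It overstates only if it is taken for the population-level effect.
- **That the authors will misreport a gap as confounding removed.** The article gives no rule for comparing the two results. Its wording invites that reading but does not commit to it.
- **That risk difference and NNT are the declared reporting scale.** They appear only in the sample-size paragraph. The firmer mismatch is between an odds ratio and a primary test that compares proportions.
- **That two tests per outcome inflate the error rate.** This needs a rule that significance in either analysis counts, and none is stated.
- **That adjustment brings a large power gain.** Against a Fisher-type exact test (about 61% in the same scenario) the gain looks large, but much of it is that test's conservatism. A mid-P or score version of the unadjusted test already reaches about 68%.

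The odds-ratio problem also applies only if the outcomes are analysed as proportions. On the mean-change metric of Table 2 the treatment difference is collapsible, and only the efficiency argument and the wrong rationale remain.

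**Conclusion.** The point holds in a limited form. The stated reason for the logistic model is wrong for a randomised comparison, and the primary test makes no use of four covariates that the protocol already names. With a real effect and prognostic covariates, the adjusted odds ratio is expected to lie further from 1 than the unadjusted one without any imbalance: about 0 to 5% for s up to 0.5 and about 20% at s = 1.0. With no effect, or with covariates that do not predict the outcome, no systematic shift of this kind arises. The efficiency forgone is roughly 0 to 8 power points for s from 0 to 1.0.

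These sizes rest on assumed response rates, a normal prognostic score and an assumed covariate strength. The protocol gives none of them, and nothing in it shows that the larger values apply. That all four variables precede allocation is inferred from Table 1. The change is worth making because it is cheap; the planned unadjusted test would not mislead if left as it is.

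**What to change.** For each primary outcome, name one primary analysis: the comparison adjusted for sex, age, co-morbidity and previous exercise, each taken as measured before randomisation.

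- If the outcome is a proportion, fit the logistic model, average the predicted response over all participants under each allocation, and report the standardised risk difference with 95% CI and the matching NNT. Specify the variance estimator, since 120 participants is a modest number for large-sample standard errors. An odds ratio may be shown beside it, labelled as conditional.
- If the outcome is mean change, as in Table 2, put the same covariates in a linear model and report the adjusted mean difference with 95% CI.
- Keep the unadjusted test as a supportive analysis.
- Replace the confounding rationale by adjustment for baseline prognostic factors, and state that a difference between adjusted and unadjusted odds ratios will not be read as confounding.

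The cost is a few sentences in the protocol or analysis plan and a few lines of code. Table 1 indicates that the covariate data are already collected. The downside is that the primary result becomes model-based, with no gain or a slight loss of precision if the covariates turn out not to be prognostic.

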### Methods to handle missing data

We do not expect many missing data since the study will be carried out within just one center and the interventional trial has a short duration (12 weeks). However, missing data may occur during the follow-up period. Thus, in the primary analysis, missing data will be replaced by “last-observation-carried-forward.” Then, multiple imputations will be used for sensitivity analyses.

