The large number of tests and measurements at multiple time points is the main strength of the study, since this allows investigation on the moderators and mediators of treatment efficacy, a point often neglected in past studies. Nevertheless, the number of tests may pose a challenge to the participants, increasing the risk of dropout at post-treatment and follow-up. Many questionnaires also pose the risk of missing data, which is another limitation of the study. Great care will be given to minimize the risk of dropout and incomplete assessment by periodic meetings with the assessors and clarifications to the participants at each test point. It should be noted the lack of accounting for clustering in the analysis, which might bring some potential limitations. However, in this study, the number of clusters is really low, and accounting for clustering, in this case, might lead to biased estimates of standard errors [27].

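### LOCF as the primary missing-data method gives week-12 dropouts zero change and carries earlier SF-12 scores to the end of follow-up, with a bias whose direction depends on when people leave

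*Protocol article*

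**What the plan says.** Under Methods to handle missing data, the protocol article expects few gaps because there is one centre and treatment is short, then adds: "However, missing data may occur during the follow-up period". It concludes that "in the primary analysis, missing data will be replaced by" LOCF. The alternative comes second: "Then, multiple imputations will be used for sensitivity analyses".

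Three other places determine what LOCF does in this trial:

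- **Primary outcomes and Table 2.** For each primary outcome, "the outcome will be assessed as a change from the baseline". All three are assessed at week 12. SF-12 alone has a second primary time point, "At week 48 (end of follow-up"), read here as visit t3.
- **Power analysis and statistical analysis.** "The analysis by treatment allocated will include all participants for which there is data at t0". The stated primary test compares proportions.
- **Treatment and Table 1.** SF-12 is measured at t0, t1 (week 12), t2 and t3. The follow-up visits are counted from the end of treatment: "t2, 24 weeks (circa 6 months) after end of trial", and t3 at 48 weeks after it.

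The Discussion is less confident about completeness. It says the number of tests may burden participants, "increasing the risk of dropout at post-treatment and follow-up". No dropout rate appears anywhere.

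**The concern.** Taken together, these passages fix how every missing primary value is filled. A participant with baseline data but no t1 value stays in the analysis with the baseline score, so the recorded change is exactly zero on SF-12, walking speed and sway. If response means reaching the expected improvements of 10%, 10% and 20%, each such participant is also a non-responder. A participant who lacks SF-12 at t3 receives an earlier score.

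Follow-up begins when the intervention stops, so a constant score is a strong assumption there, and the protocol gives no reason for it. The SF-12 result at t3 concerns lasting benefit. For those lost, LOCF supplies part of that answer by assumption.

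Some of the loss may be informative. Adverse event reporting and harms suspends participants after moderate-to-severe serious events but keeps them in the analysis by allocation. Procedure and setting withdraws those who lose eligibility because of a new treatment. Where no later data exist, LOCF gives them a value from before the event. In addition, single imputation treats each filled value as if it had been measured, so its uncertainty does not enter the standard error or the test.

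**Working it through.** The protocol states no missing-data figure to reproduce. Its sample size does not enter this check.

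**Inputs.** From the protocol: an expected effect of 0.45 SD, taken as the true between-arm difference at week 12, and a risk difference of 0.215. Assumed, because the protocol gives neither: dropout of 10% to 30%, and an effect that wanes to 0.15 SD or to zero by t3. Dropouts are assumed to follow the same course as completers unless stated otherwise.

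**Week 12, all three outcomes.** Let d be the fraction without t1 and m the true mean change in each arm. A missing t1 contributes zero, so

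LOCF difference = (1 − d_PA) × m_PA − (1 − d_C) × m_C.

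With equal dropout this is (1 − d) × 0.45:

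- 10%: 0.9 × 0.45 = 0.405 SD
- 20%: 0.8 × 0.45 = 0.36 SD
- 30%: 0.7 × 0.45 = 0.315 SD

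On the responder scale, if non-attenders count as non-responders, 0.215 becomes 0.194, 0.172 and 0.151 by the same factors.

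With unequal dropout of 30% (exercise) and 10% (control) and no true effect:

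- both arms decline by 0.2 SD: 0.7 × (−0.2) − 0.9 × (−0.2) = +0.04 SD, favouring exercise
- both arms improve by 0.2 SD: 0.7 × 0.2 − 0.9 × 0.2 = −0.04 SD, favouring control

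**End of follow-up, SF-12 only.** Let e2 and e3 be the true effects at t2 and t3. Split the missing fraction, equal in both arms, by last observed visit: a at baseline, b at t1, c at t2. Then

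LOCF effect = (1 − a − b − c) × e3 + a × 0 + b × 0.45 + c × e2.

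With 20% missing and e3 = 0.15 SD:

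| Last observed visit of those missing at t3 | Calculation | LOCF effect (SD) |
|---|---|---|
| All at t1 | 0.8 × 0.15 + 0.2 × 0.45 | 0.21 |
| Half at t1, half at baseline | 0.8 × 0.15 + 0.1 × 0.45 + 0.1 × 0 | 0.165 |
| All at baseline | 0.8 × 0.15 + 0.2 × 0 | 0.12 |
| All at t2, with e2 between 0.15 and 0.45 | 0.8 × 0.15 + 0.2 × e2 | 0.15 to 0.21 |

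The first row overstates the assumed truth by 40%, the second by 10%, and the third understates it by 20%. If the effect has vanished by t3 (e3 = 0), the first three rows become 0.09, 0.045 and 0 SD.

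If the true scores of those lost stay at their last observed value, LOCF fills in the right means and there is no bias.

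**The case against.** The case for leaving the plan alone has four parts.

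- **Attenuation is conservative.** With equal dropout, a week-12 estimate pulled toward zero does not favour a superiority claim. This stands for equal dropout only; with unequal dropout LOCF can create a difference in either direction.
- **Multiple imputation is already planned.** A divergence from LOCF would therefore be visible. This stands and limits the risk of an unnoticed wrong conclusion. The primary result would still be the LOCF one.
- **No dropout rate is documented, and constant scores may be nearly right.** Someone who stops attending early may in fact stay near baseline. This is possible, and every size above is conditional for that reason. The protocol does not argue for it.
- **Scope.** The late-follow-up problem touches SF-12 only, since walking speed and sway have no primary time point after week 12. This stands.

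A reader might infer something stronger: that LOCF necessarily favours persistence of benefit, overstates the t3 effect by 40% (by 60% with 30% missing: 0.7 × 0.15 + 0.3 × 0.45 = 0.24 SD), and holds everyone lost at the end-of-treatment score for most of a year. The documents do not support that. SF-12 is also measured at t2, so later leavers carry a score from part-way through follow-up. Those lost before t1 carry baseline, which pulls the t3 estimate toward zero. The 40% and 60% figures need every missing participant to have been last seen at t1, so they sit at the upper end under the assumed waning.

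**Conclusion.** The concern holds in conditional form. The protocol fixes LOCF as primary, and its own rules turn a missing t1 into zero change on all three primary outcomes and fill a missing SF-12 at t3 with the t2, t1 or baseline score, in that order. This can bias the primary results, and it ignores the uncertainty of the filled values.

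The direction is not fixed. At week 12, equal dropout shrinks the effect in proportion to the loss, and unequal dropout can move it either way. At t3, timing decides: under the assumed waning to 0.15 SD with 20% missing, the estimate can fall below or above the truth. These sizes rest on assumed dropout and waning rates. The understatement of standard errors was not quantified.

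**What to change.** In Methods to handle missing data, exchange the two roles.

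- **Primary:** multiple imputation by arm for the primary outcomes, using baseline, all observed visits and the covariates already listed (sex, age, co-morbidity, previous exercise). Derive responder status within each imputed dataset, then pool the difference in proportions with a standard combining rule.
- **Sensitivity:** keep LOCF, labelled as such. Optionally add a delta-adjusted imputation for SF-12 at t3, to show how far the result depends on those lost resembling those seen.

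Document the change before the group A and group B codes are unmasked. This matters because Trial status planned to end data collection in June 2020, while the protocol version is dated April 2021, so the data may already have been collected.

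The cost is small but goes beyond wording: the imputation model and pooling rule must be written down, and a pooled estimate replaces the planned exact test in the primary analysis. No new data are needed.
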